**Methods:**

The study is designed as an intervention study, documented through repeated cross-sectional surveys (2020–2024). The primary endpoint will be the sensitivity of a surveillance-response approach to detect and react to outbreaks of urogenital schistosomiasis over three years of implementation. The surveys and multi-disciplinary interventions will be implemented in 20 communities in the north of Pemba island. In low-prevalence areas, surveillance-response will consist of active, passive and reactive case detection, treatment of positive individuals, and focal snail control. In hotspot areas, mass drug administration, snail control and behaviour change interventions will be implemented. Parasitological cross-sectional surveys in 20 communities and their main primary schools will serve to adapt the intervention approach annually and to monitor the performance of the surveillance-response approach and impact of interventions. *Schistosoma haematobium* infections will be diagnosed using reagent strips and urine filtration microscopy, and by exploring novel point-of-care diagnostic tests.

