### Study setting

The implementation research study with the acronym “SchistoBreak” is a joint project with partners from the Swiss Tropical and Public Health Institute (Swiss TPH), Basel, Switzerland the Public Health Laboratory-Ivo de Carneri (PHL-IdC), Pemba, United Republic of Tanzania and the Neglected Diseases Programme of the Ministry of Health, Social Welfare, Elderly, Gender, and Children (MoHSWEGC) Zanzibar, United Republic of Tanzania. The fieldwork for the SchistoBreak study will be conducted in Pemba, an island that forms part of the Zanzibar archipelago, from March 2020 to June 2024. The population density of Pemba was 530 people/km^2^ in 2012 and the projected population for 2019 was around 500,000 people [46]. The study area will consist of 20 shehias (small administrative areas) located in the rural districts Micheweni and Wete in the north of Pemba (Fig. 2). The average population size in the study shehias is ~ 3,900 individuals per shehia [47]. To address the small-scale heterogeneity in the study area and to micro-target implementation, not the districts but each shehia will serve as one implementation unit (IU). The 20 study shehias were selected based on their isolated but contiguous location in the north of Pemba and very good documentation of *S. haematobium* prevalences in 10 among the 20 shehias from 2012 to 2020 [6, 17, 18].

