### Annual cross-sectional parasitological surveys

The annual cross-sectional surveys will be implemented in all 20 communities and their main public primary schools at sub-district shehia level. This micro-mapping approach will allow us to determine *S. haematobium* prevalences in the school-aged population, which is at highest risk of schistosomiasis, as well as in the whole community to get an accurate picture of infection levels in preschool-aged children, school-aged children, adolescents and adults. The cross-sectional surveys will serve to stratify the study area into low-prevalence and hotspot IUs and hence to micro-target the interventions according to pre-set prevalence thresholds. Moreover, the cross-sectional surveys will allow to determine and monitor the performance of the surveillance-response approach and impact of interventions over the study period. Participants of the annual cross-sectional parasitological surveys identified as infected with *S. haematobium* will be offered treatment with praziquantel (40 mg/kg using a dose pole) [50].

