### Interventions and data collection

In the study, specific intervention packages will be tailored and adapted to the local micro-epidemiology of urogenital schistosomiasis in the shehias. Low-prevalence IUs will receive tailored surveillance-response measures, consisting of active, passive and reactive case finding, treatment of *S. haematobium*-positive individuals and focal snail control. Hotspot IUs will receive a multi-disciplinary intervention package including MDA, snail control and behaviour change communication. The classification of the study shehias into low-prevalence or hotspot IUs will be based on the results of annual cross-section surveys. Initially, a shehia will be considered a low-prevalence IU if it shows an apparent *S. haematobium* prevalence < 2% in the community-based survey and an apparent *S. haematobium* prevalence < 3% in the school-based survey, based on single urine filtration microscopy. Otherwise, the shehia will be considered a “hotspot” IU (Fig. 3). Results gained over the study period will show whether these thresholds and respective intervention packages successfully sustain and accelerate the gains and prevent recrudescence of *S. haematobium* transmission in low-prevalence IUs. The thresholds will be evaluated annually in light of the results of the cross-sectional surveys and adapted if needed.

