The impact of behaviour change interventions in schools will be evaluated by assessing knowledge, attitude and practices of schoolchildren over time based on questionnaires.

The impact of the intervention approaches on the *S. haematobium* prevalence will be analysed descriptively.

The diagnostic accuracy of new PoC tests will be calculated by determining the proportion of individuals that have been correctly identified as *S. haematobium*-infected (sensitivity) and the proportion of individuals that have been correctly identified as negative (specificity) in comparison with the reference test.

The number and location of schools, madrassas, health facilities, and water bodies and the abundance of intermediate host snails of the genus *Bulinus* identified by micro-mapping of the IUs, will be analysed descriptively.

Statistical analyses will be carried out with the statistical software STATA and R.

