Despite the highlighted challenges, the SchistoBreak study will fill a critical health knowledge gap and produce important and much needed results. The study will show whether the performance of surveillance-response as intervention in low-prevalence IUs is sufficiently high to detect successfully all urogenital schistosomiasis cases and to respond with adequate interventions so that recrudescence of transmission can be prevented. It will also reveal if the *S. haematobium* prevalence in hotspot IUs can be reduced to very low levels when a comprehensive, multi-disciplinary intervention package is applied. Finally, the study will show whether new diagnostic tests are suitable for application at the PoC and outperforming current standard tests in their sensitivity and specificity to detect *S. haematobium* infections. Hence, our study will shed light on the field applicability and performance of novel adaptive intervention strategies and new diagnostic tools for schistosomiasis elimination and reveal whether progress towards interruption of transmission can indeed be achieved and sustained in the suggested way. The evidence and experiences generated by micro-mapping of *S. haematobium* infections at sub-district community level, micro-targeting of different intervention approaches, and application of novel diagnostic tools can guide future strategic plans for schistosomiasis elimination in Zanzibar and inform other countries aiming for interruption of transmission.

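### Shehias are classed on the same annual surveys used to describe the impact of their package, so regression to the mean biases the secondary prevalence results

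*Protocol article*

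**What the plan says.** On assignment, Interventions and data collection states: "The classification of the study shehias into low-prevalence or hotspot IUs will be based on the results of annual cross-section surveys". A shehia is low-prevalence only if both its community and its school survey lie under their cut-offs; otherwise it is a hotspot.

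On measuring impact, the same surveys serve again. The abstract says that they "will serve to adapt the intervention approach annually and to monitor the performance of the surveillance-response approach and impact of interventions", and the section on the annual surveys says that "the cross-sectional surveys will allow to determine and monitor the performance of the surveillance-response approach and impact of interventions over the study period". Statistical methods plans no model for this: the effect of the interventions on "prevalence will be analysed descriptively".

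On what will be read from the series, Interventions and data collection says: "Results gained over the study period will show whether these thresholds and respective intervention packages successfully sustain and accelerate the gains and prevent recrudescence" of transmission in low-prevalence units. The closing paragraph of the Discussion says that the study will reveal whether "prevalence in hotspot IUs can be reduced to very low levels when a comprehensive, multi-disciplinary intervention package is applied". The Discussion also lets a considerable rise in low-prevalence units prompt a change of the thresholds. The article describes no randomisation, concurrent control or separate baseline survey, and does not mention regression to the mean.

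**The concern.** A shehia enters the hotspot group partly because its true prevalence is high and partly because that survey happened to read high. The chance part does not recur, so the group reads lower next time even if nothing has changed. The low-prevalence group reads higher for the mirror-image reason. A single classification is enough to cause this.

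The other natural display, grouping by current class, fails differently. A low-prevalence shehia that worsens is relabelled a hotspot, so the low-prevalence group cannot show recrudescence above the threshold, and hotspots that improve drop out of their group.

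Two readings are exposed. The hotspot reduction could be overstated. Low-prevalence shehias could look as if they were recrudescing, which could prompt a threshold change for no real reason.

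**Working it through.** **Inputs from the protocol.** 20 shehias; 250 community members and 140 schoolchildren per shehia and survey; Methods cut-offs of 2% (community) and 3% (school). Check of the plan's own total: 20 × (140 + 250) = 7,800, as stated under Sample size.

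**Inputs assumed, because the documents do not give them.** Mean community prevalence 1-2%; between-shehia coefficient of variation (CV) 0.5-2, beta distributed; school prevalence 1.3 times community; no clustering; successive surveys independent given the true prevalence.

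**1. The rule in counts.** 0.02 × 250 = 5 and 0.03 × 140 = 4.2, so five positives in either survey make a hotspot.

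**2. Chance of misreading one stable shehia (exact binomial).** With true prevalence 1% (community) and 1.5% (school), P(≥5 of 250) = 0.108 and P(≥5 of 140) = 0.061. P(hotspot) = 1 − 0.892 × 0.939 = 0.16 per survey. Over four surveys (an assumed number), P(at least one change of class) = 1 − 0.162⁴ − 0.838⁴ = 0.51. At 1.5% and 2%, the figures are 0.42 and 0.86.

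**3. No-effect simulation.** True prevalences are held constant, shehias are classified on survey 1, and the same shehias are read again on survey 2. Community prevalence (%), with relative changes from unrounded means; the first four rows use 4,000 replicates and the last two 20,000:

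| Mean | CV | Hotspots of 20 | Hotspot mean, survey 1 → 2 | Low-prevalence mean, survey 1 → 2 |
|---|---|---|---|---|
| 1% | 0.5 | 3.8 | 2.16 → 1.55 (−28%) | 0.73 → 0.87 (+19%) |
| 1% | 1 | 4.4 | 2.69 → 2.34 (−13%) | 0.52 → 0.63 (+20%) |
| 1.5% | 1 | 7.1 | 3.19 → 2.95 (−8%) | 0.57 → 0.71 (+25%) |
| 2% | 1.5 | 7.2 | 4.95 → 4.78 (−3%) | 0.38 → 0.47 (+22%) |
| 2% | 0.5 | 11.4 | 2.79 → 2.52 (−10%) | 0.94 → 1.31 (+39%) |
| 2% | 2 | 5.7 | 6.38 → 6.25 (−2%) | 0.25 → 0.30 (+21%) |

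The protocol plans on 15 low-prevalence shehias. The second row (20 − 4.4 = 15.6) and the last (20 − 5.7 = 14.3) both come close, so that count does not settle the size.

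**4. Groups re-formed each year.** At mean 1%, CV 1, the hotspot mean goes from 2.69% to 2.71%, in effect no change. The fall and rise therefore come from following fixed groups. Membership, however, is then set by the outcome: in this scenario 33% of hotspots become low-prevalence and 9% of low-prevalence shehias become hotspots at the next survey by chance alone.

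**5. After the fix.** The mean over all 20 shehias stays flat (1.00% to 1.00% in this scenario). For a group fixed on survey 1, every later survey has the same expectation without an effect (2.34% for these hotspots), so change counted from survey 2 has expectation zero.

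**6. Sensitivity.** An intracluster correlation of 0.05, in households of five and classes of 20, gives −15% and +24% at mean 1%, CV 1. With almost no spread between shehias, the hotspot fall reaches 47%. Under the cut-offs in the Discussion (3% community, 2% school), community changes shrink to −1% to −7% and +1% to +8%, but school prevalence falls 5-56% in hotspots and rises 48-121% in low-prevalence shehias. These last ranges include clustering and near-zero spread.

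**The case against.** The strongest reply is that this analysis is secondary and descriptive. The primary outcome is surveillance sensitivity, and the Discussion concedes that the study is too small to show significant differences in prevalence. The layout of a descriptive table can be left to an analysis plan. The Background describes marked heterogeneity and hotspots with consistent or recurring moderate or high prevalence, which points to a wide spread, where the hotspot artefact is only a few percent. The absolute shifts are also modest: 0.61 percentage points in the first row for hotspots and at most 0.37 for low-prevalence shehias.

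Much of this stands, and it limits the point to an analysis change. It does not remove it. Low power concerns random error, whereas this shift is systematic and keeps its direction in every scenario run. The spurious rise in low-prevalence shehias stays near 20% or more across the table, even with a wide spread. Both the use of one survey series for assigning and judging, and the readings to be drawn from it, are fixed in the protocol itself.

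Four stronger readings are tempting and are not supported.

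- A reader might infer that yearly re-sorting itself makes hotspots fall and low-prevalence shehias rise. Step 4 shows that it does not.
- A reader might infer that regression to the mean could manufacture a finding that recrudescence was prevented. In followed groups it raises low-prevalence readings, so it works against that finding. Only grouping by current class could hide recrudescence, and the protocol does not say that it will group so.
- A reader might treat the two groups as trial arms. They are non-randomised strata, and no contrast between them is planned.
- A reader might see an error in not using, as a benchmark, the documented "prevalences in 10 among the 20 shehias from 2012 to 2020". Those surveys may differ in size, and the Background reports biannual mass treatment in 2012-2017, so differences from them would mix chance with another treatment schedule.

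**Conclusion.** The concern holds for the secondary, descriptive prevalence results only. Because the survey that assigns the package also supplies the starting point for change, following shehias from that survey biases hotspots downwards and low-prevalence shehias upwards. With no true change and the Methods thresholds, the community mean falls by about 2-28% in hotspots and rises by about 19-39% in low-prevalence shehias. The direction is secure. The size rests on the assumed mean, spread and school-to-community ratio, and the hotspot part is small if shehias differ widely. The hotspot reduction could be overstated, and an apparent rise in low-prevalence shehias could prompt an unneeded threshold change. The documents do not show that either conclusion would be produced by the artefact alone.

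**What to change.** In the descriptive impact analysis:

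- (a) Attribute each survey to the package received in the preceding year, not to the class that this survey assigns.
- (b) Show trajectories by baseline class, with switchers kept in their group, beside the mean of all 20 shehias. On its own this would display the artefact in full, so it needs (c).
- (c) Measure change from a baseline prevalence shrunken across all 20 shehias, or from the first survey not used to form the groups.
- (d) Name regression to the mean as a limit on the statements about thresholds and recrudescence (Interventions and data collection), threshold adaptation (Discussion) and hotspot reduction (closing paragraph of the Discussion).

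The 2012-2020 data may be shown as context, but claims should not be limited to differences from them. The cut-offs in Interventions and data collection and in the Discussion are reversed between community and school, and must be reconciled.

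The cost is analysis wording only, with no new fieldwork. Apparent hotspot reductions will look smaller, and starting from a later survey loses one interval of follow-up.

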**Fig. 3 Fig3:**
[figure not shown]
Classification of the SchistoBreak study shehias in Pemba, Tanzania, into low-prevalence and hotspot implementation units (IUs) based on adaptive *S. haematobium* prevalence thresholds

#### Surveillance-response activities in low-prevalence implementation units

In a surveillance-response system, disease-related data are continuously and systematic collected and analysed. With constant monitoring, resurgence of transmission can be detected immediately and interventions can be implemented as a response to prevent reintroduction of the disease [4, 45].

In our low-prevalence IUs, where large parts of the population are not infected with *S. haematobium*, the intervention approach is shifted from large-scale measures with high coverage towards targeted micro-interventions, i.e. from MDA in communities and schools to risk-based surveillance-response, including active, passive and reactive case finding, treatment of haematuria-positive and/or *S. haematobium*-infected individuals, and reactive snail control (Fig. 4).

**Fig. 4 Fig4:**
[figure not shown]
Interventions and components of surveillance-response activities implemented in low-prevalence shehias of the SchistoBreak study in Pemba, Tanzania

As starting point for risk-based surveillance activities, we will select the largest public primary school in each shehia, and a madrassa with a minimum of 50 children that is located at maximum 500 m away from a water body and the farthest away from the primary school to gain a differentiated picture about the *S. haematobium* micro-epidemiology at school level in each shehia [12].

For active case finding, we will visit the selected schools at least once per year, register all children of the grades 3–5 present at the first day of the visit, and provide them with an ICF for their parents to sign. Additionally, every child aged 12 years or older will be invited to sign an assent form on their own behalf. The next day, upon submission of the signed ICF and assent forms, each child will receive a plastic container and be invited to produce its own urine sample. The submitted urine samples will be examined at the point-of-care (PoC) in the school using reagent strips (Haemastix; *Siemens* Healthcare Diagnostics AG; Zürich, Switzerland) and additional PoC tests if available. Haematuria-positive and/or *S. haematobium* infected children will be treated with praziquantel (40 mg/kg using a dose pole) on the day of or day after examination.

For reactive case detection in the days following the active case detection in schools, children tested positive in the schools will be asked to show a member of the study team their house of residence and the water bodies they are using for household chores or leisure activities. Household members of the infected child who are present at the time of the visit will be offered PoC testing with reagent strips (and additional PoC tests if available) and praziquantel treatment if diagnosed positive.

Moreover, the study team will visit the HWCSs indicated by the positive children, where infected individuals might have acquired the *S. haematobium* infection or introduced transmission, and implement mobile test-and-treat stalls where testing-and-treatment with reagent strips (and additional PoC tests if available) and praziquantel, respectively, will be offered to all eligible individuals using these water bodies. In addition to praziquantel treatment (40 mg/kg using a dose pole) of positive individuals at the HWCSs, response measures will include a thorough survey for the presence of intermediate host snails and mollusciciding of the water bodies with niclosamide as described below.

All participants included in active and reactive surveillance will have at least the following data recorded: Sex, age, travel history, time of last praziquantel treatment, and water contact behaviour.

For passive case detection, individuals presenting with signs and symptoms of urogenital schistosomiasis in the health facilities located in the study shehias, will be tested for haematuria as a proxy for *S. haematobium* infection using reagent strips and treated with praziquantel (40 mg/kg using a dose pole) if positive. The study team and staff of the NTD programme of the MoHSWEGC will train staff of the health facilities about schistosomiasis transmission, prevention, diagnosis and treatment. Staff of the health facilities will record haematuria-positive individuals, their names and location of residency, and report them at least monthly to staff of the study team.

#### Intervention packages and data collection in hotspot implementation units

In the hotspot IUs, where a considerable part of the population is still infected with *S. haematobium*, we will implement a multi-disciplinary intervention package including MDA, snail control and behaviour change communication activities.

Large-scale MDA with praziquantel is the corner stone for the control and prevention of morbidity due to schistosomiasis [3, 5]. Praziquantel treatment is administered without prior diagnosis to large parts of the population living in endemic areas. In our hotspot IUs, MDA will be conducted at least annually in communities and schools by the Zanzibar NTD Programme. In communities, community drug distributors trained by the MoHSWEGC will visit all households in a door-to-door approach and offer to treat children aged 4 years or older with praziquantel (40 mg/kg) if they do not receive treatment in schools. Moreover, they will offer praziquantel to all adults that are eligible for treatment according to national treatment guidelines. In schools, praziquantel (40 mg/kg) will be provided to all children present at the day of treatment by teachers and staff of the Zanzibar NTD Programme using a dose pole [50]. The intake of tablets will be directly observed. Treatment coverage will be reported by the Zanzibar MoHSWEGC based on reports from their staff, community drug distributors, and teachers. Moreover, we will conduct our own post-treatment coverage surveys in line with the annual cross-sectional parasitology surveys in the hotspot communities and schools. When invited to submit a urine sample for annual monitoring, individuals enrolled in the survey will also be invited to respond to an ODK questionnaire, asking if they have received and swallowed the drugs provided in the MDA treatment round preceding the survey.

Snail control with the molluscicide niclsoamide is suggested by WHO as supplementary intervention to MDA in schistosomiasis-affected areas [5, 51–53]. At each identified HWCS in the hotspot IUs, a trained team will conduct regular snail surveys. While wearing wellington boots, waiders and rubber gloves to protect them from water that potentially contains infective *S. haematobium* cercariae, the team will search for snails of all species for 10 min in 20 m of the shoreline [41]. The number of snails from each collected species and data of locality, characteristics and type of water body, and observed behavioural activities will be recorded in ODK. All *Bulinus* will be taken to the laboratory for examination for *S. haematobium* infection. At all HWCSs in water bodies where *Bulinus* spp. is found, the team will apply the molluscicide niclosamide (in a concentration of 8–10 g/litre) to clear the HWCSs from infected snails and to prevent reinfection in the human population that is treated with praziquantel against schistosomiasis. Niclosamide will be sprayed to the shorelines using backpack sprayers or a petrol sprayer and the team will wear protective gear and clothing to avoid potential inhalation and eye and skin irritation [17, 54]. The amount of niclosamide used and the time and place of application will be recorded in ODK. To reduce the impact of niclosamide on other aquatic organisms, we will only focally apply the molluscicide in areas known for human water contact behaviour but not across the whole water bodies.

Behaviour change communication and community engagement is key for the success and sustainability of interventions for schistosomiasis elimination [11]. To achieve a change in behaviour, health communication, which takes local knowledge, attitudes and practices into account and integrates the communities in priority settings for decision making and planning of schistosomiasis interventions, is essential [55]. In the hotspot IUs, we will implement behavioural interventions, which were created in a human centred design approach and successfully applied in previous studies in Zanzibar [48, 56–58]. The following intervention components will be implemented: i) installation of washing platforms at a place identified together with the community in close proximity to a clean water source (i.e. pump, tap or well) to provide access and safe alternatives to washing clothes at natural water bodies; ii) training of school and madrassa teachers in classroom-based participatory teaching methods to educate children about schistosomiasis transmission and prevention using flip-charts, snail boards, blood fluke pictures, life cycle drawing, and alternative safe play methods; and iii) school-based health communication days for schistosomiasis prevention, introducing safe play methods with health education components in schools in collaboration with health teachers and classes. Within the annual cross-sectional community- and school-based surveys, we will collect KAP data including information about the perception of schistosomiasis, use of washing platforms and alternative play options, and a potential change in behaviour to assess the impact of the behaviour change and communication measures.

